#### Fit brains® training (FBT)

Participants randomized to the FBT group will be required to attend 3 formal training sessions per week, for 8 weeks, at the Djavad Mowafaghian Centre for Brain Health (UBC) or the Centre for Hip Health and Mobility (VGH). Each session will be for 60 min. Additionally, participants will be asked to complete 3 1-hour training sessions at home per week. Thus, FBT participants will complete a total of 48 h of cognitive training over the 8-week intervention.

There is currently no consensus as to the “best dosage”. However, we based our proposed dosage on the collective work by Strenziok and colleagues [6], Basak and colleagues [4], Engvig and colleagues [30], and Smith and colleagues [31]. Overall, the total number of training hours ranged from 23.5 h to 40 h, each training session ranged from 60 min to 90 min, and total intervention period ranged from 5 weeks to 8 weeks. Importantly, the study population included by Envig and colleagues [30] (i.e., older adults with subjective memory complaints) is the most similar to our target population. They employed an 8-week intervention period with one formal training session of 90 min and five home-based sessions. Each home-based session was approximately 30 min. Thus, their total number of training hours was ~ 32 h (12 h of formal training and 20 h of at home training). Notably, Envig and colleagues [30] demonstrated that after 8-weeks of training, there was significant improvement in verbal memory (i.e., long verbal delay recall) and increases in gray matter volumes. To be conservative, we increased our total number of training hours to 48 as data extracted from existing Fit Brains***®*** subscribers suggest that compared with young adults, older adults may require more frequent cognitive training to maintain benefit [32].

Fit Brains***®***, a program by Rosetta Stone Inc., offers 59 different training games, of which 38 are available on a mobile platform (e.g., iPad). The games are designed to be targeting one of six cognitive domains – focus, speed, memory, visual, problem solving, and language. The majority of the games last exactly 60 s during which individual aims to answer as many questions as quickly and accurately as possible. Other games have a set number of trials the participants have to complete before moving on to the next game. The difficulty of the game increases after each correct answer. Each game has three levels of difficulty: 1) novice; 2) intermediate; and 3) advanced.

During the FBT intervention, all participants will begin the training at the beginner level. Difficulty will increase throughout the intervention period based on their performance. At the end of each training session, FBT game progress will be saved and participants will begin the next session at that point. Each block of games will consist of 5 games. The first 5 blocks of games will be prescribed to offer an introduction to the user. After that, the sequencing of the games will be random, where each block will consist of games that need the most attention (i.e., games that showed the lowest performance), and games that will be randomly selected based on a set algorithm. Game performance will be recorded for each participant. Moreover, for their training sessions at home, participants will be asked to train at the same time of the day as their classes at VGH/UBC.

#### Exercise + fit brains® training (ex-FBT)

Participants randomized to the Ex-FBT group will be required to attend 3 formal training sessions per week, for 8 weeks, at the Djavad Mowafaghian Centre for Brain Health (UBC) or the Centre for Hip Health and Mobility (VGH). Each session will be for 1 h. Participants will start the training with a 15-min walk outside. Participants will monitor the intensity of their walk using the 20-point Borg’s Rating of Perceived Exertion [33]. For the first two weeks the participants will aim for a 10–11 on the Borg scale (i.e., between very light and fairly light). The aim for weeks 3 and 4 will be to reach for 12–13 on the Borg scale (i.e., up to somewhat hard). During the remaining 4 weeks the participants will aim for 13–14 on the Borg scale (i.e., somewhat hard). The 15-min walk will be followed by a 45-min Fit Brains***®*** training session (see FBT program, mentioned above) on the iPad. Additionally, participants will be asked to complete 3 1-h training sessions at home (i.e., 15-min walk followed by 45-min of FBT). The participants will be recording their Borg-scale scores and the number of steps they walked during their 15-min walks on a calendar that will be provided at the start of the study.

#### Balanced and toned (BAT)

Participants randomized to the BAT group will be required to attend 3 formal 1-h training sessions per week, for 8 weeks, at the Djavad Mowafaghian Centre for Brain Health (UBC) and/or the Centre for Hip Health and Mobility (VGH). Specifically, the BAT participants will complete a total of 8 h of sham cognitive training, 8 h of sham exercise training, and 8 h of education regarding brain health over the 8-week training.

We have largely designed the sham cognitive training of the BAT protocol based on the work of Baniqued and colleagues [34] who examined the nature of cognitive abilities tapped by casual online games. They identified online games that largely tapped solely into visuo-motor speed, such as Alphattack and Crashdown. Alphattack requires players to prevent bombs from landing by pressing the character specified by the approaching bomb (source: miniclip.com). Crashdown requires players to prevent the wall from reaching the top of the display by clipping on three or more adjacent same-coloured bricks to remove them (source: miniclip.com). As these online games do not significantly tap into memory abilities, we use similar online games in our BAT protocol. In addition to exercises on the iPad we include group-based games, such as drawing using both their dominant and non-dominant hand, writing captions on cartoons, and word games.

The exercise component of the BAT program will consist of once weekly balance and tone classes. The exercise program will be led by certified fitness instructors (i.e., CPR certified and NCAA certified or equivalent) and includes stretching exercises, range of motion exercises, basic core-strength exercises including kegals (i.e., exercises to strengthen the pelvic floor muscles), balance exercises and relaxation techniques. Key balance exercises include Tai Chi-based forms (i.e., Crane, Tree Pose), tandem stand, tandem walking, and single leg stance (eyes open and closed). Previous use of this protocol showed no improvements of cognitive functioning as a result of the BAT program [35]. These sessions will be held at the Centre for Hip Health and Mobility.

Additionally, once a week the participants will attend educational classes. For the first four 1-hour education sessions, participants will attend lectures relating to brain health, such as sleep and goal setting. During the remaining four weeks, participants will create their individual photo book using the iPad.

#### Adherence

Participants’ adherence to the interventions will be recorded using three methods. First, class attendance will be recorded by study team members. Second, monitoring CCT training at home will be done by the study team using the number of minutes trained per day registered by the program and provided by Rosetta Stone Inc. Third, we will ask participants to record their training minutes on a homework calendar provided by the study team.

### Outcome measures

All participants in the current study will attend three measurement sessions at VGH: baseline, trial completion, and 1-year follow-up. Each visit to VGH will be up to 3 h in duration. In addition, if interested and eligible, a subset of participants will attend two MRI scans (1.5 h per appointment) at UBC over the duration of the study (i.e., at baseline and trial completion). Our trained research staff, which will assess enrolled participants at baseline, trial completion, and 1-year follow-up, will be blinded to group allocation.

#### Descriptive measures

At baseline, general health, demographics, socioeconomic status, and education will be ascertained by a questionnaire. Descriptive measures such as age in years, standing and sitting height in centimetres, mass in kilograms, and waist and hip circumference in centimetres will be obtained.

##### Global cognitive function

Global cognitive function will be measured using both the Mini-Mental State Examination (MMSE) and the Montreal Cognitive Assessment (MoCA). The MoCA is a valid and reliable measure [29], and assesses eight cognitive domains such as attention, concentration, executive functions, memory, language and visuoconstructional skills. The total possible score is 30 points; a score of less than 26 points indicates MCI. The MoCA has with a score of 26 a 90% sensitivity to for detecting MCI [29].

##### General health, falls history, and socioeconomic status

We will administer questionnaires to obtain information about their level of education, employment status and general health information (e.g., medication, fall and fracture history).

##### Instrumental activities of daily living scale

The Lawton and Brody Instrumental Activities of Daily Living (IADL) [27] Questionnaire will be administered to assess the participants’ ability to perform tasks of daily living such as housekeeping, laundry, transportation, and management of finances. The questionnaire looks at eight different types of daily activities, and therefore it has a maximum achievable score of eight.

##### Co-morbidity

To assess the presence of any medical conditions, the functional comorbidity index (FCI) [36] will be used. In this scale, which contains 18 conditions, participants will indicate whether the condition is present currently, in the past or not at all.

##### Cognitive activity over lifetime

At baseline, we will administer a questionnaire focusing on lifetime stimulation of cognitively stimulating activities in a subset of participants [37]. This questionnaire measures the involvement in cognitively stimulating activities during their lifetime, namely at age 6, 12, 18, 40, and at their present age. Cognitively stimulating activities include visits to the library, read a newspaper, read a book, write a letter, and play a game. The involvement on all 25 items included will be rated on a 5-point scale, with 1) Once per year or less; 2) Several times per year; 3) Several times per month; 4) Several times per week; or 5) Every day or nearly every day.

#### Primary outcome: Episodic memory

Our primary cognitive outcome will be (verbal) episodic memory as measured by the Rey Auditory Verbal Learning Test (RAVLT) [38]. The RAVLT is a valid, reliable, and widely used instrument of (verbal) episodic memory. Notably, a 2013 prospective study showed that among a combination of neuropsychological, neuroimaging, and cerebrospinal fluid markers, RAVLT performance was the best individual predictor of MCI conversion to dementia [39]. For the RAVLT, a list of 15 common words (List A) will be read to participants five times. Immediately after each time, they will be asked to recall as many words as possible. After the fifth trial, an interference list (List B) will be presented, after which participants will be asked to spontaneously recall the words form the original list (List A). Then, participants will be asked to spontaneously recall the original words (List A) after a 20-min delay (i.e., long delay free recall), and finally, they will be asked to circle words from the original list (List A) in a paragraph of text containing thirty underlined words (i.e., words from the original list plus distractor words). Scores will be calculated as the total number of words recalled: 1) across the five trials (total acquisition); 2) after the interference list (recall after interference); 3) on the fifth trial minus after the interference (loss after interference); 4) at recognition (number of words correctly identified from list A); and 5) after the 20-min delay (long delay free recall – our primary RAVLT measure of interest). We will focus on changes in memory (trial completion minus baseline) over the course of the study.

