### Sample size and randomization

The required sample size for this study is calculated based on changes in the RAVLT (retention score). Specifically, we predict a mean change of 0.31 for the FBT group, a mean change of 0.40 for the Ex-FBT group, and a mean change of −0.31 for the BAT group. We made these estimates based on the work of Diamond and colleagues [58]. With a pooled standard deviation of 1.1, and alpha of 0.05, we will need 36 participants for a power of 0.80. To accommodate for a 10% drop-out rate, our total sample size comes to 120 participants (i.e., 40 FBT, 40 Ex-FBT, and 40 BAT).

Participants will be randomly allocated (1:1:1) to FBT, Ex-FBT, or BAT. The randomization sequence will be generated by an independent member of the team using computer software (www.randomization.com). Blocked randomization will be used, with a block size of 12. The group allocation will be concealed for the study coordinator. After enrolment, performed by a research assistant, and completion of the baseline assessment, the study coordinator will send a list of participant identification numbers to the independent member responsible for the randomization. This independent member will provide the study coordinator with the group assignment for the enrolled participants. After completion of baseline assessment at VGH, the participants will be informed of their group assignment. Outcome assessors will be blinded after treatment allocation.

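### The RAVLT recognition score counts correct List A words only, so it rises with willingness to circle words even when memory is unchanged (subsidiary score; primary measure unaffected)

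*Protocol article*

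**What the plan says.** The section Primary outcome: Episodic memory describes the RAVLT. It states that "a list of 15 common words (List A) will be read to participants five times". After the free-recall trials, the interference list and the 20-minute delay, participants are asked to "circle words from the original list (List A) in a paragraph of text containing thirty underlined words"; a parenthesis explains that these comprise List A words and distractors.

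Five scores follow: total acquisition, recall after interference, loss after interference, recognition, and long delay free recall. Recognition is given as the total "at recognition (number of words correctly identified from list A"). None of the five counts, subtracts or otherwise uses a distractor circled in error.

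The section marks the fifth score as the one that matters most: "long delay free recall – our primary RAVLT measure of interest". Under Sample size and randomization, the calculation rests on another RAVLT score: "The required sample size for this study is calculated based on changes in the RAVLT (retention score").

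**The concern.** A recognition test has distractors so that true recognition can be told apart from a general readiness to say yes. A score built from hits alone discards that information. Two participants with the same memory get different scores if one circles more freely, and one participant's score can rise between visits because they have become less cautious.

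This is a matter of a stated rule and not of missing detail: the article gives a scoring definition, and applying it gives a hits-only score. What is at stake is the meaning of that score. If recognition results are presented as memory, a change or an arm difference in them could not be separated from a change in response tendency.

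**Working it through.** There is no stated figure to reproduce, so the check is scoring arithmetic.

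**Inputs.** List A has 15 words and the sheet has 30 underlined words (Primary outcome: Episodic memory). Assumption: all 15 List A words are on the sheet, leaving 30 - 15 = 15 distractors. The text implies this but does not say it.

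**Limiting cases.** Let H be List A words circled and F distractors circled. The stated score is H.

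| Participant | H | F | Stated score | H - F |
|---|---|---|---|---|
| Circles all 30 words | 15 | 15 | 15 | 0 |
| Discriminates perfectly | 15 | 0 | 15 | 15 |

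The stated score cannot separate these two.

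**No memory at all.** A participant who circles a random share q of the words has expected H = 15q, and expected H - F = 15q - 15q = 0. For q = 0.25, 0.5, 0.75 and 1 the expected stated score is 3.75, 7.5, 11.25 and 15.

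**Some memory, with only the criterion moving.** Use equal-variance signal detection: H = 15·Φ(d'/2 - c) and F = 15·Φ(-d'/2 - c), where d' is sensitivity and c the response criterion (lower c means more willing to circle). The article gives neither, so the values below are assumptions chosen to show a range.

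| d' | c | H (stated score) | F | H - F |
|---|---|---|---|---|
| 1.5 | +0.2 | 10.6 | 2.6 | 8.1 |
| 1.5 | -0.2 | 12.4 | 4.4 | 8.1 |
| 1.5 | +0.5 | 9.0 | 1.6 | 7.4 |
| 1.5 | -0.5 | 13.4 | 6.0 | 7.4 |
| 1.5 | 0 | 11.6 | 3.4 | 8.2 |
| 1.5 | -1 | 14.4 | 9.0 | 5.4 |
| 3 | +0.2 | 13.5 | 0.7 | 12.9 |
| 3 | -0.2 | 14.3 | 1.5 | 12.9 |

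Three things follow.

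- At fixed d', H always rises as c falls. The direction does not depend on the assumed values.
- The size does. Moving c from +0.2 to -0.2 adds 1.8 words at d' = 1.5 but only 0.8 at d' = 3, where the score is near its ceiling.
- H - F stays constant only between criteria placed symmetrically about zero. Moving c from 0 to -1 at d' = 1.5 lowers it by 2.8 (8.2 to 5.4) while H rises by 2.8 (11.6 to 14.4). H - F is therefore only a partial remedy. In this model d' itself does not depend on c.

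**d' at the extremes.** Rates of 0 or 1 need a correction before d' can be calculated. One standard choice is to use (count + 0.5)/(15 + 1). Circling everything then gives rates 15.5/16 and 15.5/16, so d' = 0. Perfect discrimination gives 15.5/16 = 0.969 and 0.5/16 = 0.031, so d' = 1.86 + 1.86 = 3.73 (from unrounded values). The two participants whom the stated score ties are now separated.

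**The case against.** The strongest reply is that this touches nothing on which the trial concludes. Recognition is one of five RAVLT scores and is not the primary one. Free recall has no distractor list, so the problem cannot arise there. Recognition is not listed under Secondary outcomes measures, nor is it named in the aims. All of that stands, and it sets the weight of the point.

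A reader might infer that the trial will show a biased arm difference in recognition, because participants learn their allocation and the training games are played against the clock. The article does not support that. Its description of the Fit Brains games asks for accuracy as well as speed, and the control arm's sham games are also modelled on games of visuo-motor speed. Allocation is randomised and the contrasts are in change over time, so a stable personal habit of circling freely, or a practice shift common to all arms, cancels on average. Only a criterion shift that differs by arm would bias the contrast, and no evidence for one is given. Nor are the tabulated differences expected arm effects: they show what happens to a score when the criterion alone moves, under assumed values.

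It can also be said that an article condenses, and that the full protocol or the test manual may record false positives. That is possible, and the article does not say that such errors will be thrown away. But it does state how the recognition score is calculated, and recording false positives elsewhere would not change that definition.

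**Conclusion.** The point holds as a minor one about a subsidiary score. As defined, RAVLT recognition is a hit count that confounds memory with response tendency. That every word circled gives 15/15 rests on one assumption, that all 15 List A words are on the sheet. That the score rises with a more liberal criterion at fixed memory needs no particular value of d'. The sizes shown (1.8 words at d' = 1.5 and 0.8 at d' = 3, for c from +0.2 to -0.2) are illustrations under equal-variance signal detection and not predictions for this trial.

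The primary measure, its analysis and the sample size are unaffected. No bias between arms has been shown; the finding is that the score as written could not distinguish such a shift from better memory if one occurred.

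**What to change.** Before any recognition data are analysed, redefine the recognition score as a discrimination index that uses both List A words circled and distractors circled. The preferred index is d', with the correction for rates of 0 or 1 named in advance. Hits minus false positives is simpler and acceptable as an alternative, provided it is acknowledged that it removes criterion effects only in part. Report hits and false positives separately beside the index, so that a change in response tendency is visible. Confirm in the text how many of the thirty underlined words are List A words.

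The distractors circled are already on the same test sheet, so no new visit, test or participant is needed and the primary endpoint does not change. The cost is a little extra scoring. Fixing the choice beforehand also keeps it from depending on the results.

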#### Secondary outcomes measures

##### Comprehensive neuropsychological battery (iPad)

We will use the National Institute of Health (NIH) Toolbox Cognition Battery [40–42], a comprehensive neuropsychological battery with normative values. The cognitive battery of this toolbox includes tests that measure: *1) Executive Functions*: Executive functions is the capacity to plan, organize, and monitor the execution of behaviours that are strategically directed in a goal-oriented manner. The NIH Toolbox measures two components of executive functions: 1) inhibition and 2) set shifting. The NIH Toolbox focuses on the inhibition of automatic response tendencies that may interfere with achieving a goal. Set shifting is considered the capacity for switching among multiple aspects of a strategy or task. Inhibition will be measured with the NIH Toolbox Dimensional Change Card Sort Test. Set shifting will be measured with the NIH Toolbox Flanker Inhibitory Control and Attention Test; *2) Attention*: Attention refers to the allocation of one’s limited capacities to deal with an abundance of environmental stimulation. It is the foundation for all other types of mental processes. Attention will be measured with the NIH Toolbox Flanker Inhibitory Control and Attention Test*; 3) Episodic Memory*: Episodic memory refers to cognitive processes involved in the acquisition, storage and retrieval of new information. It involves conscious recollection of information learned within context. Episodic memory can be verbal (i.e., remembering a conversation or list of grocery items) or nonverbal (i.e., imagining a picture one saw a week ago). Episodic memory will be assessed with the NIH Toolbox Picture Sequence Memory Test. As a supplemental measure we will use the NIH Toolbox Auditory Verbal Learning Test (Rey)*; 4) Language*: Language refers to a set of mental processes that translate into symbols (words, gestures) that can be shared among individuals for purposes of communication. The NIH Toolbox focuses on two aspects of language: 1) Vocabulary knowledge, which will be measured with the NIH Toolbox Picture Vocabulary Test, and 2) Oral reading skill, which will be assessed by the NIH Toolbox Oral Reading Recognition Test; *5) Processing Speed*: Processing speed refers to either the amount of time it takes to process a set amount of information, or the amount of information that can be processed within a certain unit of time. It is a measure that reflects mental efficiency and is central for many cognitive functions and domains. Processing Speed will be measured by the NIH Toolbox Pattern Comparison Processing Speed Test; and *6) Working Memory*: Working Memory refers to a limited-capacity storage buffer that becomes overloaded when the amount of information exceeds capacity. Working Memory refers to the capacity of an individual to process information across a series of tasks, hold information in a short-term buffer, manipulate the information, and hold the products in the same short-term buffer. Working Memory will be assessed with the NIH Toolbox List Sorting Working Memory Test.
